#### Response to Intervention

Participants will be assessed using the following outcome measures at baseline (Week 1), immediately post-intervention (Week 8), and at 6 months after commencing the program. In addition, VAS pain will be assessed on a week-to-week basis during the first 8 weeks- that is the two assessment weeks and the 6 intervention weeks. A research assistant who will remain blind to group allocation will perform all assessments at all time-points. The primary outcomes for the study will be health status, quality of life and pain severity.

### Outcome measures

#### Western Ontario and McMaster Universities (WOMAC) Osteoarthritis index

WOMAC measures health status and assesses pain, stiffness and physical function in patients with OA of the hip or knee. For the purpose of this study the Likert (WOMAC LK3.0) format will be used. The WOMAC questionnaire is self-administered and can be completed in less than 10 minutes. Two major validity studies have shown WOMAC pain, stiffness and physical function subscales are valid and that the questionnaire is reliable and sensitive enough to detect changes in health status following a variety of interventions [13,14].

#### The Short Form 36 Questionnaire (SF-36)

The SF-36 measures quality of life and has 8 sub-components reflecting both physical and mental status. It is comprised of 36 questions, is self-administered and can be completed in approximately 15 minutes. All estimates of score reliability, from 14 separate studies, for each of the 8 sub-categories of the SF-36 exceed accepted standards for measures used in group comparisons [15]. The SF-36 has been extensively validated in many English speaking countries of the world including Australia [16]. The rationale for using both WOMAC and the SF-36 for this study is that a combined approach using both generic and knee specific measures is considered likely to prove best for knee related problems [17].

#### Visual Analog Scale (VAS)

VAS will be used to measure participants' pain severity. The VAS is a single dimension horizontal scale, which consists of a 10 cm line on which participants rate their pain from 0-10. Participants are required to place a vertical pen line through the scale at the level of their pain- 0 reflecting No Pain and 10 reflecting the Worst Pain imaginable. The VAS is well established in clinical practice for measuring pain post -surgery, following drug therapy and in response to other interventions in arthritis populations [18].

#### Modified Timed Up and Go Test

This test is a modification of the "Timed Up and Go" test (mTUG), used to assess basic functional mobility in the elderly [19]. TUG is a widely used clinical outcome tool in which the time taken to stand from sitting, walk 3 m, turn around, return to the chair and sit down is measured. This test is reliable and valid [19]. In this study, the time taken to ascend and descend a 15 cm step has been added to the outward walk, and the length of the walk has been extended to 4 m.

#### Step Test

This is a test of dynamic standing balance. It involves stepping one foot on, then off a block as quickly as possible in a set time period of 30 seconds. It has high test-retest reliability (ICC > 0.90) good concurrent validity and is sensitive to changes in performance over time [20].

#### Timed Single Leg balance Test

This is a simple test that assesses the difficulty a person has standing on one leg. The score is the total time (in seconds, to a maximum of 30 seconds) standing on one leg. It is thought that this test is a good predictor of falls in the elderly [21] and is reliable and valid (rc = 0.69) [22].

#### Arthritis Self-Efficacy Questionnaire

This is an 8-item scale. Participants are asked to complete the questionnaire by circling the number that best reflects the degree to which they are confident they can complete a described task at the present time. The score is the total of the 8 items. This questionnaire has been widely used in arthritis research and has internal consistency and reliability of 0.94 [23].

### Statistical Power

Power calculations are based on the achievement of a minimal clinically meaningful improvement [24]. With an alpha (1-tailed) of 0.05 and a sample size of 73 people in each group, this study will have power of 80% to show that the response rate for ASMP is at least as high as the response rate for OAKP. This assumes that the response rates for the ASMP and OAKP groups are equal (at 38.0%, the level of response achieved for the WOMAC function scale in our earlier RCT [10]), and that a difference of 20.0 points or less is unimportant and allows for 20% drop out.

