## Background

Chronic disease is a major concern with an ageing population, and arthritis is one of the most prevalent chronic diseases affecting 16.7% of the population in Australia [1]. Osteoarthritis is the most common form of arthritis affecting 25% of the population over the age of 65 years. The joint most frequently affected is the knee [2].

Self-management interventions are becoming increasingly popular for many chronic diseases, however the length of program and mode of delivery varies greatly between programs and between illnesses [3]. The programs may utilise a combination of health professionals (physiotherapists, occupational therapists, nurses and dieticians), trained health educators, mental health workers, and occasionally physicians, for program delivery. Other programs have lay leaders who usually deliver a scripted program. The mode of delivery also varies greatly from face to face to audiotape; group or individual contact and more recently internet based programs [4].

Comparing different self-management models is difficult as the needs of people with chronic diseases differ according to their illness. Asthma and diabetes self-management programs emphasise medication delivery and compliance, whereas self-management for other conditions may focus more on pain management strategies. Even within the broad category of arthritis, the self-management needs of people with different types of arthritis such as rheumatoid arthritis or osteoarthritis are not the same.

One widely utilised arthritis self-management program is the Stanford University's Arthritis Self Management Progam (ASMP), which is delivered by trained lay leaders [5]. The ASMP has been tested widely. The majority of studies have been conducted in the USA or UK. Many, but not all of these studies report program efficacy. Systematic reviews of self-management interventions that include the ASMP have shown there is a trend towards a small benefit for people with arthritis, but the results were not statistically significant and there was a suggestion of publication bias [3,6,7]. At this stage, it is not possible to unequivically claim that ASMP is effective.

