In view of the high prevalence of osteoarthritis of the knee and the absence of unequivocal evidence of effectiveness of ASMP, we developed an education self-management program specifically for people with osteoarthritis of the knee (OAKP). The program is delivered by health professionals with information and instruction that utilises their knowledge and skills within a self-management construct. The OAKP has been tested in a quality assurance project [8] and a randomised controlled trial (RCT) the results of which show improvements in quality of life, pain and function compared to a control group [9].

With an aging population the costs associated with arthritis are ever increasing [1]. Although cost analysis is beyond the scope of this study, it is reasonable to expect that costs will be greater when health professionals deliver self-management programs as opposed to lay leaders. Therefore it is important to establish whether delivery by health professionals results in added benefits and/or improvements in outcomes. At present both ASMP and OAKP are offered as clinical services at Arthritis WA.

Accordingly, we propose to conduct a RCT to examine the differences between OAKP, directed and delivered by health professionals, and ASMP, delivered by trained lay leaders.

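### The 80% power is for ASMP being not more than 20 percentage points below OAKP, not for ASMP being at least as good, and calling such a gap unimportant conflicts with the trial's aim

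*Protocol article*

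**What the plan says.** The Statistical Power section opens "With an alpha (1-tailed) of 0.05 and a sample size of 73 people in each group" and claims "power of 80% to show that the response rate for ASMP is at least as high as the response rate for OAKP". On the planning rates it says: "This assumes that the response rates for the ASMP and OAKP groups are equal". The common value is borrowed from a previous trial of the program, being set "at 38.0%, the level of response achieved for the WOMAC function scale in our earlier RCT". The section also declares: "a difference of 20.0 points or less is unimportant and allows for 20% drop out".

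Other sections point the opposite way. The Hypothesis section expects a greater proportion of OAKP than ASMP completers to improve, and the aim in the Abstract is worded in the same direction. Given the likely higher cost of health professionals, the Background says "it is important to establish whether delivery by health professionals results in added benefits and/or improvements in outcomes".

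The Data Analysis section compares the proportions with a Chi-square test and infers significance at a 1-tailed p below 0.05. It does not mention the 20 points.

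**The concern.** The power claim is stronger than the calculation behind it. Showing that one response rate is at least as high as another is not the same as showing that it is at most 20 points lower, and the sample size delivers only the second. On a planning rate of 38%, 20 points is a large allowance.

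The word unimportant adds to this. An OAKP advantage of 10 or 15 points in responders is the kind of added benefit that the Background says must be established, yet the power section dismisses it in advance.

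What is at stake is the reading of a non-significant Chi-square test. Set beside a claim of 80% power to show that ASMP is at least as good, and a statement that gaps up to 20 points do not matter, such a result could be reported as parity between lay-led and professional-led programs. The design does not support that.

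**Working it through.** **Inputs (Statistical Power section; the Abstract gives the total of 146):** response 38% in both groups, difference allowed 20 points, 1-tailed alpha 0.05 (z = 1.645), power 80% (z = 0.842), 73 per group, drop-out 20%.

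**1. Reproducing the 73.** Non-inferiority of two proportions with unpooled variance:

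n = 2 × 0.38 × 0.62 × (1.645 + 0.842)² / 0.20² = 72.8, rounded up to 73 per group.

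Other readings miss it:

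| Reading | n per group |
|---|---|
| Non-inferiority, one-sided 0.025 | 93 |
| Non-inferiority, Farrington-Manning | 72 |
| Non-inferiority, continuity-corrected | 83 |
| Superiority, 38% v 18%, one-sided 0.05 | 62 |
| Superiority, 38% v 58%, one-sided 0.05 | 77 |

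So the 20 points are percentage points of response, used as a non-inferiority margin for ASMP.

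**2. What the 80% refers to.** With 73 per group analysed:

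- SE = √(2 × 0.38 × 0.62 / 73) = 0.0803
- Power = Φ(0.20/0.0803 − 1.645) = 80.1%

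This is the chance of excluding an ASMP deficit of 20 points or more when the true rates are equal.

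**3. Drop-out.** The 73 in step 1 contains no allowance for drop-out. If 20% are lost and not analysed, 73 × 0.80 = 58.4, about 58 per group:

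- SE = √(2 × 0.38 × 0.62 / 58) = 0.0901
- Power = Φ(0.20/0.0901 − 1.645) = about 72%

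**4. Size of the margin.** 20/38 = 53% of the planning response. At the margin ASMP responds at 38 − 20 = 18%.

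**5. Share of the OAKP effect lost at the margin.** The untreated response c is not in the article, so it is an assumption. The 38% is taken as the OAKP rate. Share lost = 0.20/(0.38 − c):

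| Assumed c | Share lost |
|---|---|
| 0% | 53% |
| 10% | 71% |
| 15% | 87% |
| 18% | 100% |

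**6. What a non-significant Chi-square leaves open.** If OAKP truly responds at 38% and ASMP at 28%, the 1-tailed test has about 36% power with 73 per group and about 31% with 58. A real 10-point advantage would therefore usually be non-significant.

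Using the planning SE as an approximation, the test is non-significant for observed OAKP advantages up to about 1.645 × 0.0803 = 13 points with 73 per group. The matching upper confidence limit at that edge is about 2 × 1.645 × 0.0803 = 26 points. A non-significant result need not exclude even a 20-point deficit.

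**The case against.** The strongest reply is that no planned analysis tests ASMP against the margin. The hypothesis is OAKP superiority and the test is an ordinary Chi-square, so the trial cannot formally meet a 20-point margin. That stands. It means the margin criticism does not apply whichever direction is tested: under a superiority test there is no margin, and the 20 points could at most be read as a target difference. It does not make the power sentence correct, and it leaves the misreading of a non-significant test open.

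Second, the 20-point allowance is disclosed in the next sentence, so a careful reader can see the condition. That is fair. For the same reason, noting that power for a zero margin under equal rates is only 5% carries little weight, because that is alpha in any such design. But the sentence as written still names a conclusion that the calculation does not support.

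Third, the choice of margin is a judgement. Preserving a fraction of the effect is only one approach, and fuller reasoning may sit in the full protocol. This also stands, and no smaller margin is asked for here.

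A reader might infer that meeting the margin would allow ASMP to have lost the entire OAKP effect, especially since the Background says "it is not possible to unequivically claim that ASMP is effective". The article does not support that outright. The 38% is a response rate that is not tied to a named arm, and losing everything requires an untreated response of at least 18%, which is not reported.

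**Conclusion.** The point holds as a misstated power claim with a consequence for interpretation. On the plan's own inputs, the 80% belongs to ASMP being not more than 20 percentage points lower, and only if 73 per group are analysed; it is about 72% with 58. The margin is 53% of the planning response and excludes only ASMP rates below about 18% when OAKP is at 38%. Describing gaps of that size as unimportant contradicts the stated purpose of finding added benefit from OAKP.

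The power figures assume true rates of 38% in both groups and a normal approximation with unpooled variance. The 58 assumes that drop-outs are not analysed. Nothing here shows that the whole OAKP effect would be lost, or that a particular smaller margin is required.

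**What to change.** 1. In Statistical Power, restate the claim as power to show that the ASMP response rate is *not more than 20 percentage points lower than* the OAKP rate. Label it as a non-inferiority calculation, separate from the OAKP superiority hypothesis, and give the power for the number expected to be evaluable (about 72% at 58 per group; 80% only if all 73 are analysed).
2. Replace the statement that "a difference of 20.0 points or less is unimportant" with one saying that 20 points is the margin used for sizing, and that a loss from 38% to 18% would be more than half of the response.
3. In Data Analysis, for each responder endpoint, report the OAKP minus ASMP difference with its confidence interval alongside the Chi-square test.
4. State that neither a non-significant Chi-square test nor an interval that excludes only a 20-point deficit will be reported as ASMP being equivalent to, or as good as, OAKP.

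The cost is some wording and one interval per responder endpoint, with no extra participants or procedures. The downside is a weaker permitted conclusion for ASMP and a less favourable stated power.

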**Methods/Design:**

The effectiveness of the programs will be compared in a single-blind randomized study.

*Participants: *146 participants with established OA knee will be recruited. Volunteers with coexistent inflammatory joint disease or serious co-morbidities will be excluded.

*Interventions*: Participants will be randomised into either OAKP or ASMP groups and followed for 6 months.

*Measurements*: Assessments will be immediately before and after the intervention and at 6 months. Primary outcome measures will be WOMAC and SF-36 questionnaires and a VAS for pain. Secondary outcomes will include balance, tested using a timed single leg balance test and a timed step test and self-efficacy. Data will be analysed using repeated measures ANOVA.

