### Hypothesis

A greater proportion of people with osteoarthritis of the knee that complete the OAKP will report clinically meaningful improvements in pain, knee function and quality of life, at 8 weeks, and 6 months compared to those who complete the ASMP.

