### Data Analysis

Data will be analysed in a blinded manner using SPSS v17 for Macintosh. Treatment groups will be examined for comparability at baseline using unpaired t-tests or Chi-squared test as appropriate. Main comparisons between treatment groups will be performed using an intention to treat analysis. For all subjects who complete the 6-month measurements, previous values will be carried forward to replace any interim missing values.

The proportion of participants achieving minimal clinically meaningful improvement in the health status, quality of life and pain will be computed for each group at each observation time. The effect of the treatment, in terms of the proportion showing minimal clinically meaningful improvement will be examined using Chi-square test. Separate analysis will be conducted for each of the outcome variables of interest.

Further, participants will be classified as overall responders or non-responders. A favourable response to treatment (responder) will be defined according to scenario D of the OMERACT-OARSI criteria [25]. That is, an improvement of ≥ 50% in pain or function and an absolute change of ≥ 20 points on a 100 point scale, OR an improvement of at least 2 of the following: An improvement of ≥ 20% and an absolute change of ≥ 10 in two of pain, function and global health. The proportion of participants achieving responder criteria will be computed for each group at each observation time. The effect of the treatment, in terms of the proportion of responders will be examined using Chi-square test.

Finally, repeated measures ANOVA will be used to examine the differences between groups over time. Statistical significance will be inferred at a 1-tailed p < 0.05. Results will not be adjusted for multiple comparisons as all outcomes of interest have been nominated a priori and such adjustment would likely render all findings of interest non-significant, despite their clinical importance [26]. Separate analysis will be conducted for each of the outcome variables of interest.

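### The sample size is set for non-inferiority of ASMP, but the aim and hypothesis are superiority of OAKP, so the stated 80% power describes no analysis in the document

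*Protocol article*

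**What the plan says.** The Abstract aim asks whether OAKP achieves and maintains improvement in more participants than ASMP. The Hypothesis section gives the same direction: "A greater proportion of people with osteoarthritis of the knee that complete the OAKP will report clinically meaningful improvements", at 8 weeks and 6 months, compared with ASMP.

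The Statistical Power section answers a different question. The trial is said to have "power of 80% to show that the response rate for ASMP is at least as high as the response rate for OAKP". It continues: "This assumes that the response rates for the ASMP and OAKP groups are equal", at 38.0%, the WOMAC function response in an earlier trial, and "a difference of 20.0 points or less is unimportant". It adds that the number allows for 20% dropout.

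Data Analysis compares the groups in three ways. The treatment effect "in terms of the proportion showing minimal clinically meaningful improvement will be examined using Chi-square test", overall responders are also compared by chi-square, and repeated measures ANOVA looks for differences between groups over time. Significance is one-tailed at 0.05. The 20-point figure does not appear in that section.

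**The concern.** A power statement should give the probability that the planned test supports the planned hypothesis when a stated effect is true. Here the hypothesis says OAKP is better, the power statement aims to show that ASMP is no worse, and the tests look for a difference. The power calculation assumes no difference between programs, which is the condition under which the hypothesis is false.

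The result is meant to inform whether delivery by health professionals, expected to be more costly, brings added benefit. If the chi-square test is not significant, the power statement offers apparent support for calling ASMP as good, but no described analysis tests that. If the test is significant, the reader has no stated superiority effect against which to judge how well the trial was designed to find it.

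**Working it through.** **Inputs from the document.** "With an alpha (1-tailed) of 0.05 and a sample size of 73 people in each group" (Statistical Power); "146 participants with established OA knee will be recruited" (Abstract), so 1:1 allocation; 38% in both arms, 20-point margin and 20% dropout (Statistical Power); one-tailed p < 0.05 (Data Analysis).

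**1. Reproduce the plan's figure as non-inferiority.**

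n per arm = (z₀.₉₅ + z₀.₈₀)² × 2p(1−p) / margin²
= (1.645 + 0.842)² × 2 × 0.38 × 0.62 / 0.20² = 72.8, so 73.

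Power at 73: 0.20 / √(2 × 0.38 × 0.62 / 73) − 1.645 = 0.845, giving 80.1%. Both stated figures are matched.

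**2. Try superiority formulas instead (80% power, 20-point gap).**

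| Rates | One-sided 0.05 | Two-sided 0.05 |
|---|---|---|
| 58% v 38% | 77 per arm | 97 per arm |
| 38% v 18% | 62 per arm | 78 per arm |

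None gives 73. The number comes from the non-inferiority calculation, so the wording of the power statement is not a slip.

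**3. Evaluable numbers.** The 72.8 in step 1 contains no dropout inflation. With 20% loss, 73 × 0.8 = 58.4, or about 58 per arm. Non-inferiority power at 58 is 71.7%.

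**4. Superiority power of the existing sample at the plan's own one-tailed 0.05.** The document states no superiority effect. As an assumption, I borrow its 20-point figure and place the 38% first in ASMP and then in OAKP. The one-tailed chi-square is treated as the equivalent z test:

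power = Φ{ [d − 1.645 × √(2p̄(1−p̄)/n)] / √([p₁(1−p₁) + p₂(1−p₂)]/n) }

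- 58% v 38%, p̄ = 0.48, n = 73: (0.20 − 1.645 × 0.0827) / 0.0810 = 0.790, so 78.5%.
- 58% v 38%, n = 58: (0.20 − 1.645 × 0.0928) / 0.0909 = 0.521, so 69.9%.
- 38% v 18%, p̄ = 0.28, n = 73: (0.20 − 1.645 × 0.0743) / 0.0725 = 1.073, so 85.8%.
- 38% v 18%, n = 58: (0.20 − 1.645 × 0.0834) / 0.0813 = 0.773, so 78.0%.

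Power depends strongly on the assumed gap. With ASMP at 38% and n = 73, it is 57.0% for a 15-point advantage and 33.5% for 10 points.

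**5. Under the plan's own assumption (38% in both arms).** The superiority test rejects at about its alpha: 5% nominally, 5.3% by exact calculation at 73 per arm.

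**The case against.** **Non-inferiority may be what was meant.** The Background and Discussion give a cost rationale, and a non-inferiority question about the cheaper program would fit it. The Aims section says only that effectiveness is compared. This stands in part. A reader might infer that the power section is simply the wrong one, but the document does not settle which section should yield. It does settle that they disagree, because the Abstract aim and the Hypothesis both state a direction.

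**The margin analysis may be in an unseen plan.** A statistical analysis plan or fuller protocol could contain a confidence interval set against the margin. The claim is therefore limited to the analyses described in this article. An unseen analysis would still leave the power objective in conflict with the hypothesis printed beside it.

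**The 80% is nearly right for superiority anyway.** At 73 evaluable per arm and a 20-point gap, one-tailed power is 78.5% to 85.8%. This is true but coincidental. The article does not state that effect, it labels a gap of that size unimportant, and the power falls to about 70% to 78% after the stated dropout.

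**Power equal to alpha under equal rates is true of any superiority test.** This is correct. Step 5 does not measure how weak the trial is. It shows only that the stated assumption cannot support a power figure for the stated hypothesis.

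**The plan never says a null result shows equivalence.** This is also correct. The risk comes from the power statement and is not a declared intention.

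**Conclusion.** The point holds. The Statistical Power section sizes a one-sided non-inferiority comparison in favour of ASMP. The aim and hypothesis state superiority of OAKP, and the described analyses are tests of difference that make no use of the margin. The 80% is arithmetically sound for 73 evaluable per arm, but it belongs to a question that the described analyses do not test.

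For superiority at the plan's one-tailed 0.05, an assumed 20-point advantage gives about 79% to 86% power with 73 evaluable per arm and about 70% to 78% with 58. The range reflects which arm has the 38%. The Group allocation section calls the source trial an OAKP trial, which makes 38% for OAKP plausible, but the article gives no ASMP rate.

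A reader might infer that the trial is badly underpowered or must recruit more. The document does not support that, because the required number depends on a superiority effect it never gives. A reader might also infer that a two-sided test is required here. Sidedness is a separate matter: the article fixes one-tailed 0.05 in both Statistical Power and Data Analysis.

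**What to change.** Reconcile Statistical Power with the Abstract aim, Hypothesis and Data Analysis, in one of two ways.

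**If superiority is the aim, as the aim and hypothesis now say:** remove the claim about ASMP being at least as high. State the superiority power of the existing sample at one-tailed 0.05, declare the assumed rates as assumptions, and give the figure for both 73 and about 58 evaluable per arm. Remove or explain the statement that 20 points or less is unimportant, since it conflicts with using a 20-point target. Report the risk difference with its confidence interval, and say that a non-significant chi-square does not show that ASMP is as good.

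**If non-inferiority of ASMP is the aim:** rewrite the aim and hypothesis, and add to Data Analysis a comparison of the confidence interval with the margin. Justify the margin, since 20 of 38 points is about 53% of the assumed response (20/38). Quote the power after dropout (71.7% at 58 per arm).

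The cost is wording and a less favourable power figure. No extra participants or data are needed for the correction. Keeping 80% superiority power after 20% loss for a 20-point gap would take 78 (38% v 18%) to 97 (58% v 38%) randomised per arm at one-tailed 0.05, but that is a separate decision.

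### The 73 per group is the number needed with no drop-out, so the stated 20% allowance is not in it; after 20% loss the power is about 72%, not 80%

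*Protocol article*

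**What the plan says.** The Statistical Power section of the protocol article frames the calculation as non-inferiority. The section opens its calculation "With an alpha (1-tailed) of 0.05 and a sample size of 73 people in each group" and claims "power of 80% to show that the response rate for ASMP is at least as high as the response rate for OAKP". Both programs are assumed to have a true response rate of 38.0%, the level seen for WOMAC function in the group's earlier trial. The last clause gives the margin and the allowance for loss together: "a difference of 20.0 points or less is unimportant and allows for 20% drop out".

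The abstract (Methods/Design) gives the enrolment target: "146 participants with established OA knee will be recruited".

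The Data Analysis section calls the main comparisons intention to treat. Its only stated rule for missing values carries earlier values forward to fill interim gaps in people who do complete the 6-month assessment.

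**The concern.** A sample size that allows for drop-out should exceed the evaluable number the test needs. Here the enrolled number equals the evaluable number that the stated inputs require, so the claimed allowance appears never to have been applied.

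This section is the article's only justification for enrolling 146 people. If the allowance is absent, readers are told that attrition is covered when it is not. At the loss the authors themselves expect, the trial would miss the stated power even for the question it was sized for, and an inconclusive result could be over-read.

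**Working it through.** **Inputs**, all from the Statistical Power section unless noted:

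- one-tailed alpha 0.05, z = 1.6449
- power 80%, z = 0.8416
- response rate 0.38 in each group, so the variance term is 2 × 0.38 × 0.62 = 0.4712
- margin 0.20
- drop-out 20%
- 73 per group; 146 recruited in total (abstract), and 146 / 2 = 73

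**Step 1. Reproduce the plan's figure without drop-out.** Unpooled normal approximation for non-inferiority of two proportions:

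n = (1.6449 + 0.8416)² × 0.4712 / 0.20² = 72.83, rounded up to **73 per group**.

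Power at 73 evaluable: Φ(0.20 / √(0.4712/73) − 1.6449) = **80.1%**.

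The plan's 73 and 80% are both recovered with no inflation.

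**Step 2. Apply the stated drop-out.**

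- Enrolment needed to keep 80%: 73 / (1 − 0.20) = 91.25, so **92 per group**, 184 in total, and 184 − 146 = 38 more than planned.
- The cruder inflation, multiplying by 1.2, gives 73 × 1.2 = 87.6, so 88 per group. That is still well above 73.

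**Step 3. Power if 73 are enrolled and 20% are lost.** Expected evaluable number: 73 × 0.80 = 58.4 per group.

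Φ(0.20 / √(0.4712/58.4) − 1.6449) = **72.0%**.

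| Evaluable per group | Power, normal approximation | Power, exact enumeration |
|---|---|---|
| 58 | 71.7% | 71.6% |
| 59 | 72.3% | 73.7% |
| 73 | 80.1% | 79.8% |

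**Step 4. Does another non-inferiority formula give 73 after inflation?**

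| Method | n before drop-out | n after dividing by 0.8 |
|---|---|---|
| Unpooled, one-sided 0.05 | 73 | 92 |
| Farrington-Manning, one-sided 0.05 | 72 | 90 |
| Continuity-corrected, one-sided 0.05 | 83 | 104 |
| Unpooled, one-sided 0.025 | 93 | 117 |

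None does. Working backwards, if 73 already included the cruder inflation, the base would be 73 / 1.2 = 60.8. Power at 61 evaluable per group is 73.6%, not 80%.

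**The case against.** Two objections deserve an answer.

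**The derivation of 73 is not shown, and other routes land near it with an allowance.** Take 38% against 18%, the rates at the margin, with a one-sided alpha of 0.05 and 80% power. The arcsine method gives 60.5 per group, and 60.5 × 1.2 = 72.6, so 73. The unpooled formula gives 59.2, and 59.2 / 0.8 = 74.0. Under those rates the power at 58.4 evaluable would be about 79% to 80%. However, both routes use unequal rates, whereas the section states that the rates are equal. The arcsine route also reaches 73 only by multiplying by 1.2, which does not restore the required number after a 20% loss. What stands is a limit on inference: the article cannot show how the authors reached 73. It does show that the inputs they report give 73 with nothing added.

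**The main comparisons are intention to treat, so the analysed number might stay at 73.** If drop-outs stayed in the denominator, for example as non-responders, the loss of numbers behind the 72% would not occur, although the response rates would change. The article states no rule that keeps 6-month drop-outs in the responder comparison; its carry-forward rule covers only people who complete. An allowance for drop-out is also only needed if drop-outs reduce the evaluable number. Under the alternative reading none was needed and none is in the 73, so the sentence would still be wrong. What stands is that the 72% is conditional on drop-outs not contributing.

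**Conclusion.** The concern holds. On the stated inputs, 73 per group is the evaluable number for 80% power, and 146 recruited is exactly twice that. The words "allows for 20% drop out" are therefore not true of this sample size.

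With 20% lost from each group and drop-outs outside the comparison, power is about 72% (71.7% at 58 per group, 72.3% at 59). If the two programs are truly equal, the chance of failing to show it within the 20-point margin rises from about 20% to about 28%. The 72% rests on that loss and that handling of drop-outs; the error in the sentence does not.

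This conclusion concerns only the non-inferiority calculation as written. The Hypothesis section states superiority of the OAKP, and correcting the drop-out term does not tell the reader the power for that question.

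**What to change.** Correct the sentence in the Statistical Power section in one of two ways:

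- state that 73 evaluable participants per group give 80% power, with no allowance for drop-out; or
- state that 73 randomised per group leave about 58 evaluable after 20% drop-out, with power of about 72%, and say that this assumes drop-outs do not enter the responder comparison.

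Either costs one sentence and a less favourable stated power, with no extra enrolment and no change to the analysis. If the sponsor instead wants 80% power after 20% loss, the target becomes 92 per group (184 in total), 38 more participants, and the abstract's recruitment figure must change with it.
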